## Abstract

**Background:**

The evidence for choices between antipsychotics for children and adolescents with schizophrenia and other psychotic disorders is limited. The main objective of the Tolerability and Efficacy of Antipsychotics (TEA) trial is to compare the benefits and harms of quetiapine versus aripiprazole in children and adolescents with psychosis in order to inform rational, effective and safe treatment selections.

**Methods/Design:**

The TEA trial is a Danish investigator-initiated, independently funded, multi-centre, randomised, blinded clinical trial. Based on sample size estimation, 112 patients aged 12-17 years with psychosis, antipsychotic-naïve or treated for a limited period are, 1:1 randomised to a 12- week, double-blind intervention with quetiapine versus aripiprazole. Effects on psychopathology, cognition, health-related quality of life, and adverse events are assessed 2, 4, and 12 weeks after randomisation. The primary outcome is change in the positive symptom score of the Positive and Negative Syndrome Scale. The recruitment period is 2010-2014.

**Discussion:**

Antipsychotics are currently the only available pharmacologic treatments for psychotic disorders. However, information about head-to-head differences in efficacy and tolerability of antipsychotics are scarce in children and adolescents. The TEA trial aims at expanding the evidence base for the use of antipsychotics in early onset psychosis in order to inform more rational treatment decisions in this vulnerable population. Here, we account for the trial design, address methodological challenges, and discuss the estimation of sample size.

**Trial registration:**

ClinicalTrials.gov: NCT01119014

## Background

Early onset psychosis (EOP, onset before age 18 years) is considered grave and may have worse outcomes compared to adult onset psychosis [1,2]. In adults, antipsychotics have proven more effective than placebo in improving psychotic symptoms and preventing relapse [3,4] and comparisons of benefits and harms of different antipsychotic drugs have been assessed in large meta-analyses [5,6]. In children and adolescents with EOP, placebo-controlled trials and, especially, active-controlled trials are limited [7-10].

Seven primarily industry-sponsored randomised placebo-controlled trials covering a total of 1198 children and adolescents with schizophrenia have been published: six trials investigated effects of the second-generation antipsychotics (SGAs) aripiprazole [11], olanzapine [12], risperidone [13], paliperidone [14], quetiapine [15], and ziprasidone [16] in adolescents with schizophrenia. One trial compared the first-generation antipsychotic (FGA) haloperidol with placebo in children with schizophrenia [17]. Six of these seven trials showed superiority of the antipsychotic compared with placebo. The ziprasidone trial was terminated due to lack of efficacy. Only 12 randomised clinical trials (RCTs) compared different antipsychotics in the treatment of EOP. Five RCTs were open-label head-to-head studies investigating olanzapine versus (vs) risperidone (n = 44, including adolescents and young adults aged 16-28 years) [18]; risperidone vs olanzapine vs quetiapine (n = 30) [19]; olanzapine vs quetiapine (n = 50) [20]; quetiapine vs risperidone (n = 22) [21]; and olanzapine vs risperidone (n = 25) [22]. Six RCTs were double-blind, head-to-head trials investigating clozapine vs haloperidol (n = 21) [23]; clozapine vs olanzapine (n = 39) [24]; clozapine vs olanzapine (n = 25) [25]; risperidone vs olanzapine vs haloperidol (n = 50, including both non-affective and affective psychotic disorders) [26]; olanzapine vs risperidone vs molindone (n = 119) [27]; and a double-blind RCT (n = 126) comparing paliperidone vs aripiprazole [28]. One older RCT assessed thiothixene vs thioridazine (n = 21) [29]. Across these trials, only clozapine has shown superiority compared with other antipsychotics (haloperidol or olanzapine) when used for treatment-resistant early onset schizophrenia [23-25]. Each of these head-to-head RCTs included small to medium size patient samples (total n = 572). In comparison, a recent meta-analysis of antipsychotic drugs in adult schizophrenia included data from 43,049 patients [6]. It is problematic that the use of antipsychotics in EOP to a large extent is based on extrapolations from trials conducted in adults, considering that the prevalence of adverse reactions and treatment resistance may be higher in children and adolescents [20,30-32].

Outcome of antipsychotic treatment in psychosis is typically assessed with validated psychopathology scales and unsolicited adverse effect reporting, supplemented with usually few validated adverse events scales and some physical health parameters. However, other potential outcomes are also relevant for the prognosis of EOP, including cognitive deficits [33-41] and health-related quality of life (HRQoL) [42]. It has been difficult to observe consistent effects of antipsychotics on these outcomes in adults [38,39,43-45], and in the few studies conducted in EOP [46-50].

The Food and Drug Administration (FDA) has approved the use of quetiapine and aripiprazole in the treatment of schizophrenia from age 13 years, but no trials have compared the two drugs in EOP [51]. Here, we present the trial protocol of an investigator-initiated and independently funded RCT comparing the effects of quetiapine vs aripiprazole in EOP.

### Objectives

The primary objective of the TEA (Tolerability and Efficacy of Antipsychotics) trial is to compare quetiapine vs aripiprazole in the treatment of EOP with regards to efficacy (psychopathology, cognition, HRQoL) and tolerability (motor adverse events (AEs); metabolic AEs; hormonal AEs; cardiac AEs, suicidal ideation; and other AEs) in a randomised, blinded design.

### Hypotheses

The TEA trial tests the null hypothesis that there are no significant differences between quetiapine vs aripiprazole in EOP after 12 weeks of treatment on the primary outcome, Positive and Negative Syndrome Scale (PANSS) positive symptoms (PANSS-P) [52]. Due to different receptor profiles and prior data [7,8,11,15] we expect specific differences in secondary outcomes primarily reflected in adverse effect assessments with aripiprazole causing more akathisia than quetiapine; and quetiapine causing more sedation, weight gain, and metabolic adverse effects than aripiprazole.

## Methods/Design

### RCT design

The TEA trial is a Danish investigator-initiated, independently funded, randomised, blinded, multi-centre superiority trial. Patients (n = 112) are randomised to a 12 weeks intervention period with quetiapine vs aripiprazole.

### Participants

Patients are recruited from seven child- and adolescent mental health centres covering all Danish university clinics nationwide (University Hospitals of Copenhagen (4 centres), Southern Denmark (1 centre), Aarhus (1 centre), and Aalborg (1 centre)).

#### **
*Patient inclusion criteria*
**

Inclusion criteria: 1) Children and adolescents aged 12-17 years (both inclusive), both sexes; 2) in- or outpatients; 3) meeting the criteria for ICD-10 [53] psychosis diagnoses (non-organic, non-drug-induced): F20 (Schizophrenia), F22 (Persistent delusional disorders), F23 (Acute and transient psychotic disorders), F24 (Induced delusional disorders), F25 (Schizoaffective disorders), F28/F29 (Other/Unspecified nonorganic psychosis), F30.2 (Mania with psychotic symptoms), F31.2 (Bipolar affective disorder, current episode manic with psychotic symptoms), F31.5 (Bipolar affective disorder, current episode severe depression with psychotic symptoms), F32.3 (Severe depressive episode with psychotic symptoms), or F33.3 (Recurrent depressive episode, current episode severe with psychotic symptoms). The diagnosis is verified by Schedule for Affective Disorders and Schizophrenia for School-Age Children Present and Lifetime version (K-SADS-PL) 4 weeks after inclusion into the trial [54]; 4) clinical indication for antipsychotic treatment; 5) presence of psychotic symptoms scoring ≥4 on at least one of the following PANSS items: P1 (delusions), P2 (conceptual disorganisation), P3 (hallucinations), P5 (grandiosity), P6 (suspiciousness/persecution), or G9 (unusual thought content); as well as a total PANSS score >60 points; 6) antipsychotic-naïve or limited exposure (i.e., no more than 12 months in the past year for psychosis, or no more than 1 week lifetime for any non-psychotic indication); and 7) written informed consent by caretakers.

#### **
*Patient exclusion criteria*
**

Exclusion criteria: 1) Compulsory treatment; 2) drug-induced or organic psychosis; 3) severe chronic somatic illness or a history of severe head trauma; 4) pregnancy or lactation; 5) substance dependence (ICD-10 F1X.2 dependence syndrome) within the last year; 6) allergy towards the investigational drugs or lactose intolerance; 7) lack of informed consent.

### Randomisation and blinding

Randomisation of patients to treatment is carried out centrally by the Copenhagen Trial Unit at the Capital Region Pharmacy using a computer-generated allocation sequence with a block size unknown to the investigators. To optimise the comparability between treatment groups, randomisation is stratified by two factors: PANSS-P score (i.e., ≤20 points or >20 points), and age (i.e., 12-14 years or 15-17 years). Computer-generated and sealed allocation sequence lists are prepared according to the stratification variables and the trial medication packages are distributed accordingly. The interventions are blinded to participants, caregivers, outcome assessors, statisticians, conclusion drawers, as well as all investigators and staff involved in the trial, except for the pharmacy personnel who pack and distribute the two study drugs and the data managers at the Copenhagen Trial Unit.

### Interventions and assessments

During the first 9 days, the assigned antipsychotic is uptitrated in fixed dose steps, with slower titrations and dose adjustments if clinically indicated (see below). The target doses are quetiapine 600 mg/day vs aripiprazole 20 mg/day. However, if needed, dosing is flexible (quetiapine: 50-800 mg/day; aripiprazole 2.5-30 mg/day). Beneficial and harmful effects are assessed at three time points during the intervention period, i.e., weeks 2, 4, and 12.

### Post-randomisation exclusions

Patients are excluded if there is a significant worsening of their clinical state during the course of the trial (i.e., increases of 20% or more from baseline on the PANSS total score).

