### Outcomes

The primary outcome is positive symptoms measured on the PANSS-P scale. Secondary outcomes are 1) other psychopathology measures assessed on PANSS negative and general scales; Dimensions of Psychosis Instrument (DIPI) [55]; Clinical Global Impressions - Severity/Improvement/Efficacy (CGI-S/I/E) [56]; Global Assessment of Psychosocial Disability (GAPD) [53]); 2) cognition and cognitive daily functioning measured on Brief Assessment of Cognition in Schizophrenia (BACS) Global Score [57]; Schizophrenia Cognition Rating Scale, Danish version (SCoRS-DK) [58]; Behavioural Rating Inventory of Executive Functions (BRIEF) [59]); 3) HRQoL measured on KIDSCREEN-52 [60]; 4) adverse reactions measured on ‘Udvalget for Kliniske Undersøgelser’ Side Effect Rating Scale (UKU) [61]; Abnormal Involuntary Movement Scale (AIMS) [62]; Simpson Angus Scale (SAS) [63]; Barnes Akathisia Rating Scale (BARS) [64]; cardiac adverse reactions (such as QT-interval prolongation on Electrocardiography (ECG)); somatic events (blood pressure, pulse, body weight, height, body mass index, abdominal circumference, abnormal laboratory test results (fasting blood glucose, insulin and lipid levels, prolactin, other general blood tests)); suicidal ideation measured by K-SADS-PL (specific items); adherence (daily registration by caretakers or staff and antipsychotic blood levels); substance use (interview and urine testing) (Table 1).

**Table 1 T1:** TEA RCT, schedule for outcome assessments during 12 weeks of blinded intervention

**Assessments**	**Inclusion (week 0)**	**Follow-up (week 2)**	**Follow-up (week 4)**	**Follow-up (week 12)**
**Psychopathology and adverse reactions rating scales** PANSS, DIPI, CGI-S, CGI-I, CGI-E, GAPD, UKU, AIMS, SAS, and BARS	X	X	X	X
**Suicidal ideation** K-SADS-PL specific items	X	X	X	X
**Cognition, cognitive daily and executive function** BACS, SCoRS-DK and BRIEF	X			X
**Somatic examination** Standard clinical examination, blood pressure, pulse, weight, height, BMI, and abdominal circumference.	X	X	X	X
**Health-related quality of life** Questionnaire: KIDSCREEN-52	X			X
**Laboratory tests** (see list below)	X		X	X

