### Data analysis

Data will be blinded during the analysis, and the blinding will not be broken before two conclusions are drawn (i.e., the first assumes treatment A to be quetiapine and treatment B to be the aripiprazole; the second is based on the reverse assumption, i.e., that treatment A is aripiprazole and B is quetiapine) [82]. A detailed protocol for the statistical analysis plan will be presented in a separate paper. In short, the primary analysis will be according to the modified intention-to-treat principle [83] with adjustment for the protocol specified stratification variables [84]. Data missingness will be investigated and if deemed necessary, generally when missingness is not completely at random, a suitable multiple imputation method will be used [85-92]. The data will be analysed with a two-sided statistical testing and p-values will be assessed at a significance level of 5% with correction for multiple testing according to Holm [93]. Covariates considered relevant to adjust for in comparative analysis will be incorporated in the statistical model. We aim at analysing the data as trajectories including multiple assessments whenever possible.

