Another challenge encouraging us to update our sample size estimation was the slow participant recruitment, as also demonstrated in other RCTs in child- and adolescent psychiatry [27]. Our original sample size (based on an estimated PANSS-P SD of 7.4, a MIREDIF of 3.5 and power of 90%) of n = 188 was expected to be recruited during a 2 year period from mid-2010. This expectation was based on available statistical data from the Danish Psychiatric Central Register concerning the incidence of first-episode psychosis in the involved geographical areas, whereof we expected to be able to randomise 50%. However, the recruitment turned out to be slower, primarily due to administrative difficulties in implementing the trial protocol in all centres. Adjustment of the sample size during the course of a clinical trial is a potential strategy to meet such challenges. We chose to update our sample size estimation by 1) adjusting the estimated SD of our primary outcome measure, change in PANSS-P, to a score of 5.7, based empirically on new relevant data from additional studies in the field that were relatively large and happened to report lower SDs, 2) changing the power from 90% to the more conventionally used 80%, and 3) lowering the MIREDIF from 3.5 to 3.0. As a result of these adjustments our updated sample size estimation still aims at detecting a difference between the two interventions on the primary outcome measure of a medium effect size of around 0.5, which is considered clinically relevant. At present, we have included all n = 112 patients during a recruitment period of 3½ years, and the last randomised patients are terminating the blinded treatment.

We believe that the updated sample size estimation is based on as accurate variables as possible, with the same conservative value for α, a value of SD, which is based on the most updated empirical body of evidence, and relevant estimates for the expected MIREDIF and effect size. We expect one agent being superior to the other by a score of 3 on the change in PANSS-P, which is in line with Arango et al. [20]. If the mean SD turns out to be higher than 5.7, we will use the statistical principles of interim analysis [114] to control for random errors. We will analyse the data by using the intention-to-treat principles and application of multiple imputations for missing data as outlined above.

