### Strengths and limitations

The strengths of the TEA trial is the RCT design, the central handling of randomisation procedures, the comprehensive blinding, and the use of intention-to-treat analysis, all reducing the risks of bias [126,127]. The use of validated methods to assess benefits and harms increases the credibility of findings. The nationwide involvement of child and adolescent health centres aims at strengthening the generalizability of the TEA trial results.

A higher variation of the primary outcome measure than a priori expected may limit the statistical power of the trial. Furthermore, since sample size estimation is based on the primary outcome measure only, the effect sizes of differences between interventions on secondary measures are not a priori predicted, and we may not have enough power to conclude on all of our data. On the other hand, important adverse effects are likely to have larger effect sizes than the primary efficacy outcome, providing very likely sufficient power for these comparisons.

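### The post-randomisation exclusion for a 20% rise in PANSS total is not reconciled with the modified intention-to-treat and intention-to-treat statements, and could remove treatment failures from the primary analysis

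*Protocol article*

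**What the plan says.** Four places in the protocol article bear on this.

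- **Post-randomisation exclusions:** "Patients are excluded if there is a significant worsening of their clinical state during the course of the trial". The threshold is "increases of 20% or more from baseline on the PANSS total score".
- **Outcomes:** "The primary outcome is positive symptoms measured on the PANSS-P scale". PANSS-P is one of the subscales that make up the PANSS total. Table 1 schedules PANSS at weeks 0, 2, 4 and 12.
- **Data analysis:** "the primary analysis will be according to the modified intention-to-treat principle". The same paragraph foresees multiple imputation where judged necessary and, where possible, analysis of trajectories over several visits. It refers the detail to a separate statistical paper.
- **Discussion:** Sample size estimation says "We will analyse the data by using the intention-to-treat principles", with multiple imputation. Strengths and limitations names "the use of intention-to-treat analysis, all reducing the risks of bias".

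No place says what patients meeting the rule are excluded from, or how the rule fits with the analysis-set statements.

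**The concern.** The trigger is a score measured after randomisation that includes the primary outcome. If it decides who is analysed, the analysis set is selected on the outcome. When one drug is worse, more of its patients cross the threshold, its worst scores disappear, and the arms look more alike. In a superiority trial that biases the estimate towards no difference and costs power. It also hides treatment failure, which a head-to-head trial should show.

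The rule carries no visit limit. Read literally, it also covers worsening first recorded at week 12, where it could remove an endpoint already observed.

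The article uses two names for the analysis set. The one in Methods is the looser, and the Discussion takes credit for the stricter. A reader cannot tell whether the rule is the modification.

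**Working it through.** **Plan's own figure.** Inputs from the article: two-sided alpha 0.05, power 80%, SD 5.7, difference 3, 112 patients (about 56 per arm).

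- Table 4: N = 4(z_α/2 + z_β)²(SD/MIREDIF)², with the leading factor rounded to 31: 31 × (5.7/3.0)² = 111.9, so 112. Unrounded it is 113.3.
- Power at 56 per arm: 79.5% by the normal approximation (78.8% by the t-test). The figure reproduces.

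**Loss of numbers alone.** The article gives no exclusion rate, so these fractions are assumptions. With the 3-point difference intact, dropping 5%, 10% or 20% of each arm leaves power of 77.5%, 75.2% or 70.2%.

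**Selective loss, if patients meeting the rule are dropped from the analysis.** Assumptions not in the article:

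- baseline PANSS total 82, so the threshold on the raw score is 0.20 × 82 = 16.4 points
- SD of total change (s) 16 to 27
- correlation (r) of total change with PANSS-P change 0.6 to 0.8
- mean total change 2.5 times mean PANSS-P change
- bivariate normal changes, with the rule applied at one visit.

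For an arm with mean PANSS-P change μ, let a = (16.4 − 2.5μ)/s and λ = φ(a)/Φ(a). Then:

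- fraction dropped = 1 − Φ(a)
- mean of those kept = μ − 5.7rλ
- SD of those kept = 5.7√(1 − r²(aλ + λ²))
- power = Φ(d/SE − 1.96), using the reduced numbers and the reduced SD.

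Worked case, mean changes −8 and −5, s = 18, r = 0.8:

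| | Better arm | Worse arm |
|---|---|---|
| a | (16.4 + 20)/18 = 2.022 | (16.4 + 12.5)/18 = 1.606 |
| λ | 0.053 | 0.116 |
| Dropped | 2.2% | 5.4% |
| Mean kept | −8.24 | −5.53 |
| SD kept | 5.50 | 5.32 |
| n kept | 54.8 | 53.0 |

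The difference is 8.24 − 5.53 = 2.71. The pooled SD is 5.41, so SE = 5.41 × √(1/54.8 + 1/53.0) = 1.042. Power = Φ(2.71/1.042 − 1.96) = Φ(0.64) = 74%.

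Over the whole range of s and r:

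| Mean PANSS-P changes | Dropped, better vs worse arm | Difference left | Power |
|---|---|---|---|
| −9.5 vs −6.5 | 1-7% vs 2-11% | 2.7-2.9 | 72-77% |
| −8 vs −5 | 1-9% vs 4-14% | 2.6-2.8 | 71-75% |
| −5 vs −2 | 4-14% vs 9-21% | 2.5-2.7 | 66-70% |

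The Discussion cites mean changes of 6.2 to 9.6 in trials of these drugs. The first row lies within that range, the second is close to it, and the third assumes much less improvement.

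**The case against.** The strongest reply is that the article never says these patients leave the analysis. *Excluded* may mean only that blinded treatment ends. The planned imputation and trajectory analysis point that way, since they matter chiefly when patients with missing later scores stay in. Because the trigger is an observed score, a likelihood model or imputation that keeps the triggering visit can deal with the loss under missing at random. The definition of *modified* can also properly be left to the statistical paper.

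Much of this stands. It rules out several stronger readings that a reader might infer:

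- **That intention-to-treat is shown to be broken.** Removal from the analysis is one possible reading of the rule and its heading, not a stated plan.
- **That failures are shown to be removed unequally by arm.** The same rule applies to both blinded arms, and no worsening rates are given. Loss is unequal only if worsening is. If the drugs are equivalent, the rule creates no difference and costs only precision.
- **That the week-4 K-SADS-PL check removes further patients.** The article says the diagnosis is verified then. It does not say that unconfirmed patients are dropped.
- **That power falls to 65% in the expected case.** That figure comes from putting a difference of 2.55 into the calculation with the full 112 patients and SD 5.7. Deleting the worst scores lowers both the number and the SD, and 2.55 lies below the range found for improvements like those cited.

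The reply does not remove the conflict in the text. The article prints an exclusion rule tied to the outcome, a modified analysis set, and an unqualified intention-to-treat claim, with nothing to connect them. The protection under missing at random also needs the triggering visit to be kept, which no section promises.

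**Conclusion.** The concern holds as an unresolved conflict that puts the primary comparison at risk. It is not a demonstrated bias. The exclusion rule, the modified intention-to-treat statement and the two intention-to-treat statements must be reconciled.

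The cost arises only if patients meeting the rule are dropped from the analysis and one drug is truly worse. In that case a 3.0-point difference shrinks to about 2.6 to 2.9, and power goes from about 79% to about 70-77% for mean changes within or near the cited range. With much smaller improvement, power is about 65-70%. These ranges rest on the assumed baseline total, SD of total change, correlation and ratio of total change to PANSS-P change. The direction, towards no difference, does not depend on the exact values as long as the worse arm worsens more often.

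**What to change.** Limit the change to the analysis set and the data kept:

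1. State that all randomised patients, including those who meet the exclusion rule, are in the primary analysis set in the arm to which they were randomised.
2. Keep every observed PANSS score: the visit that triggered the rule and any later score, including week 12.
3. Handle later missing scores by the planned trajectory model or multiple imputation. Add a sensitivity analysis that assumes no later benefit for these patients.
4. Report the number with a rise of 20% or more in PANSS total by arm.
5. Use one term for the analysis set in Data analysis, in the Discussion's Sample size estimation, and in Strengths and limitations.

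The cost is wording plus one sensitivity analysis. The article reports that all 112 patients are included and that the last are finishing blinded treatment, and the analysis is to be done blinded, so this can be settled before any result is known. The downside is that some week-12 scores will be off study drug or imputed, so the estimate describes assignment to a drug and not continued use of it. Nothing here bears on when study drug should stop.
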